### Randomization and blinding

Randomization will be performed by independent investigators with the SAS (9.3, SAS Institute Inc., Cary, NC, USA) software. The resulting list of random numbers has been placed into sequentially numbered, sealed, opaque envelopes. Based on the information obtained from the envelopes, consecutively enrolled participants will be randomly assigned, in a 1:1 ratio, to stereotactic lesioning or classical epileptogenic zone resective surgery. Patients who are assigned to stereotactic lesioning surgery will be also assigned in a 4:1 ratio to a subgroup of RF-TC and a subgroup of LITT. The same group of neurosurgeons at different centers (three groups in total) will be responsible for different procedures for each participant.

Researchers and clinical research coordinators participate in the grouping process. Clinical research coordinators are responsible for informing patients, but they are not involved in the patient assessment and treatment process. All subjects and clinicians will be aware of the trial group assignments before surgical treatment, outcome assessors. However, outcome assessors and statisticians will not be aware of the subgroups of subjects

### Interventions

All three groups of participants will receive routine epilepsy care and antiepileptic drugs throughout the study. Participants will regularly take ASMs, which will be tailored according to the patient’s age, seizure type, drug interactions, physical health, and other factors. Medication adjustments will be handled by two experienced senior neurologists. Participants will be asked not to adjust the type and dose of medication and not to undergo other procedures throughout the observation period, unless there is a sudden exacerbation and they withdraw from the study. The surgical technique for LITT, RF-TC, and resective surgery is similar to that described previously [20, 24–27]. The main adverse events of the study will be mainly related to perioperative complications. Necessary medications and surgical procedures will be employed to prevent such damages. There is no anticipated additional harm and compensation for trial participation.

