## Abstract

**Background:**

This protocol describes the design of a multicenter randomized controlled trial of robot-assisted stereotactic lesioning versus epileptogenic foci resection. Typical causes of focal epilepsy include hippocampal sclerosis and focal cortical dysplasia. These patients usually present with drug resistance and require surgical treatment. Although epileptogenic foci resection is still the most commonly used treatment for such focal epilepsy, there is increasing evidence that epileptogenic focus resection may lead to neurological impairment. The treatment of epilepsy with a robot-assisted stereotactic lesioning mainly includes two new minimally invasive surgical methods: radiofrequency thermocoagulation (RF-TC) and laser interstitial thermal therapy (LITT). Seizure-free is less likely to be achieved by these two procedures, but neurologic preservation is better. In this study, we aimed to compare the safety and efficacy of RF-TC, LITT, and epileptogenic foci resection for focal drug-resistant epilepsy.

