## Background

Epilepsy is a common disease of the nervous system causedby different causes, with spontaneous, recurrent, and unpredictable seizures as the main characteristics. It also has numerous neurobiological, cognitive, and psychosocial consequences [1]. Several epidemiological studies show that the incidence of epilepsy is 5.5–7.3‰ [2–4]. Drug therapy is the preferred treatment for epilepsy at present. However, about 30% of patients are still unable to control their seizures after continuous treatment with two or more appropriate anti-seizure medications (ASMs), which are defined as drug-resistant epilepsy (DRE) [5, 6]. In cases of drug failure, optimal seizure control usually requires neurosurgical intervention targeting the epileptic foci. Epilepsy surgery can be divided into diagnostic surgery (subdural electrode implantation, stereotactic multicontact electrode implantation, etc.), resective surgery (lesion resection, lobectomy, hemispherectomy, etc.), and palliative neuromodulation surgery (vagus nerve stimulation, deep brain stimulation, etc.) [7–9]. Patients with drug-resistant focal epilepsy can benefit from the removal or disconnection of a circumscribed brain region to achieve complete seizure control or at least reduce disabling seizures. Among carefully selected patients, the proportion of individuals who are seizure-free after surgery ranges from 50 to 80% [10, 11].

In the 1960s, Talairach and Bancaud innovatively took the anterior and posterior connections of the brain as the benchmark for homogenization, which created the stereotactic surgery technique in neurosurgery [12]. In recent years, with the rapid development of robot-assisted technology, the stability, accuracy, and economy of stereotactic surgery have made great progress. With the assistance of a robot, the implantation time of multicontact electrodes has been shortened to 3–5 min per electrode, and the accuracy of entry point, angle, and other parameters has been significantly improved; thus, the safety of surgery has been improved [13, 14]. Today, stereoelectroencephalography (SEEG) provides a unique approach to exploring the pathophysiology of epilepsy and pinpointing the epileptogenic network that no other noninvasive examination can provide. At the same time, because of the advantages of nerve function protection, stereotactic lesioning accounts for an increasing proportion of surgical treatment in major epilepsy medical centers around the world.

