### Procedures for withdrawal or discontinuation

Participants can withdraw at any time. Eligible participants will receive three follow-up visits at 3, 6, and 12 months after surgery or until any of the following events occur.DeathEnd of the study periodLoss to follow-up: defined as referral to an epilepsy center that is not included in the study, or refusal to continue follow-up, or cannot be contacted by phone calls or WeChat for at least three times.Other epilepsy surgical treatment is required due to the conditionInvestigator considers it necessary for the participant to terminate the study

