#### Secondary outcomes

Engel classification at one-year follow-up after surgery.The proportion of participants with neurologic impairment after surgery, primarily determined by the change in NI.SHH scale score at each post-operative visit and neurological physical examination findings at each post-operative visit.Spectrum distribution and Epileptogenic Index change of video EEG at each post-operative visit.Participants’ quality of life after treatment. Evaluation will be performed at each post-operative visit by the Quality of Life in Epilepsy-89 scale (adults > 17 years) and the Quality of Life in Epilepsy-31 scale (children 4–16 years).Epilepsy-related medical costs at each post-operative visit.

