### Statistical analysis

Statistical analysis will be mainly performed by researchers from Sanbo Brain Hospital, Capital Medical University, using the SAS 9.3 (SAS Institute Inc., Cary, NC, USA) software. Take the test level *α* = 0.05. The Kolmogorov-Smirnov test will be used to test whether the variables will be normally distributed. Measurement data conforming to normal distribution will express as mean ± standard deviation (‾X ± s), and measurement data not conforming to normal distribution will be expressed as interquartile range *M* (Q25, Q75). The *t*-test will be used to compare the normal distribution of continuous variables. The rank sum test will be used to compare the continuous variables that do not conform to the normal distribution. The chi-square test will be used to compare the categorical data. Univariate and multivariate methods will be used to analyze the preoperative and operative factors associated with seizure-free. Analysis of the primary outcome will be by intention-to-treat.

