### Sample size

According to earlier studies and the previous work of our research team, the effective rates of stereotactic EEG-guided RF-TC, MRI-guided stereotactic LITT, and resective surgery are similar, and the rates of postoperative neurological impairment are 2%, 2%, and 11%. We expect to use a one-sided 95% confidence interval, a noninferiority limit of 10%, and an expected withdrawal rate of 20%. Therefore, we expect to enroll a total of 240 patients in this study. Patients will be recruited from outpatient and MDT with strict inclusion criteria.

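### Follow-up ends on sudden exacerbation or further epilepsy surgery, so the 1-year seizure outcome would be lost selectively in patients who do badly

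*Protocol article*

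**What the plan says.** Two sections of the protocol article set the rule.

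- **Interventions.** Participants are to leave drug type and dose alone and "not to undergo other procedures throughout the observation period, unless there is a sudden exacerbation and they withdraw from the study". The same paragraph says "Medication adjustments will be handled by two experienced senior neurologists".
- **Procedures for withdrawal or discontinuation.** "Eligible participants will receive three follow-up visits at 3, 6, and 12 months after surgery or until any of the following events occur". The listed events include a need for other epilepsy surgery, an investigator's decision to end participation, and loss to follow-up. Loss to follow-up is defined to include referral to an epilepsy center outside the study.

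The outcomes affected are these.

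- The primary outcome is each participant's percent reduction in monthly seizure frequency from baseline (Primary outcome). It is assessed at 3 months, 6 months and 1 year (Abstract, Methods; Table 1).
- "Engel classification at one-year follow-up after surgery" is the first secondary outcome. Table 1 schedules it at the 12-month visit only.

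Statistical analysis adds: "Analysis of the primary outcome will be by intention-to-treat". The sample size allows for "an expected withdrawal rate of 20" percent, without saying why patients would leave.

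**The concern.** A patient who has a sudden exacerbation, or who needs a second operation, is in most cases one whose first operation did not control the seizures. Under these rules such a patient keeps the visits already made but contributes nothing afterwards. The 12-month visit is the one most often lost, and Engel class is lost entirely.

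The patients left at 1 year would then be a favourable selection, and each arm would look better than it is. The comparison between arms is also exposed. On the two lesioning procedures, the Abstract says: "Seizure-free is less likely to be achieved by these two procedures, but neurologic preservation is better". If exacerbation or reoperation is therefore commoner after lesioning, more of its failures disappear and the 1-year comparison tilts towards lesioning. Patients and clinicians know the allocation (Randomization and blinding), so decisions to reoperate or withdraw could also differ by arm. The Sample size section works with a noninferiority limit of 10%, and hiding a deficit in the new treatment is the costly error in that setting.

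A lesser point is wording. Interventions gives two neurologists the task of adjusting drugs but links a drug change to leaving the study. The withdrawal section names neither exacerbation nor a drug change, although its investigator-decision item could cover them. Centres may apply this differently.

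**Working it through.** **The plan's own figure.** The total of 240 cannot be properly reproduced, because the article states neither a power nor an effective rate. The point does not depend on it. Only the expected loss is needed: 0.20 × 240 = 48 patients, or 24 of 120 per arm if loss is equal.

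**Inputs.**
- From the article: N = 240, 1:1 allocation to lesioning or resection, 20% withdrawal. For seizure freedom, Background says that "the proportion of individuals who are seizure-free after surgery ranges from 50 to 80" percent; this is used here as the completer rate r.
- Assumed: only observed 1-year values are analysed; a share s of withdrawals are failures (not seizure-free); the other withdrawals resemble completers.

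**1. Inflation within an arm.** True rate = r × (1 − 0.20 × s), so inflation = 0.20 × s × r.

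| s | r = 0.50 | r = 0.80 |
|---|---|---|
| 0.25 | 2.5 points | 4.0 points |
| 0.50 | 5.0 points | 8.0 points |
| 1.00 | 10.0 points (true 40%) | 16.0 points (true 64%) |

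**2. Difference between arms, same completer rate in both.** The reported difference is 0 in every case below. The true rate in an arm is r × (1 − loss × s).

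- 24/24 split: loss is 20% in each arm, so the true difference is also 0 and there is no bias.
- 30/18 split (lesioning/resection): loss is 30/120 = 25% and 18/120 = 15%.
  - s = 1, r = 0.50: 0.50 × 0.75 = 37.5% against 0.50 × 0.85 = 42.5%, a true difference of −5.0 points.
  - s = 1, r = 0.80: 60% against 68%, a true difference of −8.0 points.
  - s = 0.5: true differences of −2.5 points (r = 0.50) and −4.0 points (r = 0.80).

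**3. The same effect starting from assumed true rates.** Let p be the true success rate and f the share of failures whose follow-up stops. Completer rate = p / (p + (1 − p)(1 − f)). Take p = 50% for lesioning and 60% for resection, a true difference of −10 points.

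- f = 0.4 and 0.1: 0.50/0.80 = 62.5% and 0.60/0.96 = 62.5%. The reported difference is 0. Loss is 20% of the lesioning arm and 4% of the resection arm.
- f = 0.2 in both: 55.6% and 65.2%. The reported difference is −9.7 points.
- All of a 20% loss in each arm being failures: 0.50/0.80 = 62.5% and 0.60/0.80 = 75%. The reported difference is −12.5 points.

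**4. Mean percent reduction (the primary outcome).** In one arm, observed mean − true mean = loss share × gap, where the gap is the mean among remaining patients minus the mean among lost patients. With the same gap in both arms, the bias between arms = difference in outcome-related loss × gap. For assumed gaps of 30 to 90 points:

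- difference 0: no bias;
- difference 5 percentage points: 0.05 × 30 = 1.5 to 0.05 × 90 = 4.5 points;
- difference 10 percentage points: 0.10 × 30 = 3 to 0.10 × 90 = 9 points.

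**The case against.** The strongest reply has four parts.

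*The exacerbation sentence is ambiguous.* It may mean only that the restriction no longer binds someone who has already withdrawn. That is a possible reading, but it changes little. On either reading, the only route to a drug change or a procedure for exacerbation runs through leaving the study. The further-surgery trigger is explicit in any case.

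*This is a condensed article, and missing data belong in the SAP.* The handling of missing values can indeed be left there, and reoperation could be scored as failure without later seizure counts. But the article does more than stay silent: it states that visits end. An SAP can choose an imputation method, but it cannot supply counts that the follow-up rule stops collecting. The phone contact under Data management supports scheduled visits and does not reach patients whose follow-up has ended.

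*Size and direction are assumed.* This stands. The 20% is not broken down by reason, and death, refusal and failed contact contribute to it. The 30/18 split and the 30 to 90 point gaps are illustrative, and the larger figures concern seizure freedom, not the primary outcome. Equal shares of failures lost barely move the difference (−10 to −9.7), and one equal-loss scenario works against lesioning (−12.5). The Sample size section itself assumes similar effective rates.

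*Continued follow-up can mislead too.* If a failed thermocoagulation patient then has a resection, later counts credit lesioning with the benefit of resection. This is correct, and it is why a rule for further surgery must accompany continued follow-up.

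**Conclusion.** The concern holds and should be fixed. A stated rule stops measuring seizure frequency because seizure frequency is poor, and this undercuts the intention-to-treat commitment at 1 year. Inflation within each arm follows whenever failures are preferentially lost and only observed values are analysed; it is 2.5 to 16 points of seizure freedom over the range examined. Bias between arms is conditional. It can be zero, it can hide a true lesioning deficit of 2.5 to 8 points under a 30/18 split, or it can run the other way. Bias towards lesioning needs more outcome-related loss in that arm, which the Abstract makes plausible but nothing in the article quantifies. Values from visits before the event are kept, so the 3- and 6-month results suffer less. The medication wording is secondary, a mismatch and not a contradiction.

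**What to change.** 1. In Interventions, delete the clause that ties exacerbation to leaving the study.
2. In Procedures for withdrawal or discontinuation, state that an exacerbation, a drug change or further epilepsy surgery ends neither the visits nor outcome collection unless consent is withdrawn. Where possible, treat referral to an outside center the same way.
3. Record each such event with its date and reason.
4. Keep these patients in the intention-to-treat primary analysis with their observed seizure counts at 3, 6 and 12 months. For visits after further epilepsy surgery, apply a rule stated in advance, for example treatment failure, so that a rescue resection is not credited to lesioning. Because the primary outcome is a percentage, the rule must name the value assigned.
5. Say whether the medication rule bars only changes made by the participant or also changes by the two neurologists. Which changes are clinically acceptable is for the investigators to decide.

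The cost is a short amendment to two sections, plus the visits of patients who would otherwise have stopped. The visits and the drug record are already in Table 1. The amendment does alter treatment policy to the extent that drug changes for exacerbation would occur within the trial, and some outcomes will then reflect later treatment as well as the randomised operation. The article reports recruitment as ongoing, so the change is best made early: outcomes not collected cannot be reliably restored later.

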#### Arm 1: Resective surgery group

The resective surgery that patients will undergo in this study means the resection of epileptogenic foci. Patients with temporal lobe epilepsy will undergo standard anterior temporal lobectomy, and those with extratemporal lobe epilepsy will undergo lesionectomy and corticectomy with different lobes. The surgical techniques are roughly based on the previous research related to the resective surgery [28–30]. Surgical procedures for all patients will be recorded by the operating neurosurgeon.

#### Arm 2: Stereotactic EEG-guided RF-TC group

Patients enrolled in the stereotactic EEG-guided RF-TC group will undergo multicontact electrodes (RSDE-16/RSDE-12, Sinovation, China) implantation. After the intracranial electrodes are implanted, additional CT scans will be obtained to confirm their locations. Intracranial EEG recordings will be monitored to locate the epileptogenic zone. RF-TC will be performed on the contacts of the epileptogenic zone using a radiofrequency lesion generator (model R-2000B M1, BNS, China). A test heating will be performed first, and the patient will be monitored by EEG for 1 day. If the patient does not experience any unacceptable complications, RF-TC will be proceeded (3 W, 120 s). After RF-TC, the patient will be monitored by EEG for at least 1 night. The electrodes will then be removed, and the skin will be closed.

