**Methods:**

This is a multicenter, three-arm, randomized controlled clinical trial. The study will include patients older than 3 years of age with epilepsy who have had medically refractory seizures for at least 2 years and are eligible for surgical treatment with an epileptogenic focus as determined by multidisciplinary evaluation prior to randomization. The primary outcome measure is seizure outcome (quantified by seizure remission rate) at 3-month, 6-month, and 1-year follow-up after treatment. Postoperative neurologic impairment, spectrum distribution change of video electroencephalogram, quality of life, and medical costs will also be assessed as secondary outcomes.

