### Participant selection

The study is expected to enroll 240 participants. All participants will be recruited from the outpatient clinics of three centers and will be fully explained at the time of recruitment and will sign a written informed consent form. Minor participants and their legal guardians will also be fully explained about the study, and the written informed consent will be signed by their legal guardians.

Patients will be eligible for inclusion in the study only if all of the following criteria are applied:Age ≥ 3 years at enrollmentMeets the ILAE guidelines for the diagnosis of drug-resistant epilepsy with persistent disabling seizures (at least 1 or more per month); seizures persist after 2 years of standardized treatment with at least one or more first-line antiepileptic drugsWith a definite epileptogenic zone by preoperative comprehensive evaluation, which belonged to focal epilepsy, and are suitable for stereotactic RF-TC, stereotactic LITT, or resective surgeryAbility to understand and speak Mandarin Chinese

Patients with the following conditions will be excluded:

Epileptogenic foci cannot be accurately located or multiple epileptogenic foci are suspected after a comprehensive evaluation, which are not suitable for the operation included in this study.Pregnant or breastfeedingContraindications to surgeryHistory of previous operation for the purpose of treating epilepsyInclusion in any other clinical trialOther conditions that the researcher thinks he/she is not suitable to participate in the study

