#### Arm 3: MRI-guided stereotactic LITT group

After local anesthesia, skull markers will be implanted and then a CT scan will be performed, and the results of which will be fused with T1-weighted MRI by the Sinoplan (V2, Sinovation, China) software for robot navigation registration. After general anesthesia, the patient’s head will be fixed with a magnetic resonance compatible head frame and connected to the operating table and SR1 stereotactic robot (Sinovation, China). After registering the surgical plan, the surgical field will be sterilized, the skull will be drilled, the dura will be punctured, and a probe will be used to ensure smooth access to the fiber-optic cannula. The guide screw will be installed, the cooling jacket containing the fiber will be placed at the planned depth, and an MRI scan will be performed to determine the location of the fiber. After confirming that the position of the optical fiber is in line with the plan, a series of ablations will be performed with real-time visualization using MRI thermometry to ensure that target structures reached temperatures between 60 and 80 °C. If necessary, the optical fiber will be withdrawn for repeated ablation. After all ablations are completed, the scope of ablation will be determined by scanning enhanced nuclear magnetic resonance. Then, the laser fiber, cooling catheter, and anchor bolt will be removed, the skin will be closed, and the patient will be awakened.

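### Only the RF-TC arm is described as locating the zone by intracranial EEG after allocation, and the stopping rules could then end outcome follow-up for patients the intention-to-treat analysis needs

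*Protocol article*

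**What the plan says.** **Eligibility.** The abstract's Methods paragraph admits patients "with an epileptogenic focus as determined by multidisciplinary evaluation prior to randomization". Participant selection requires a definite zone from the preoperative work-up and lists as an exclusion "Epileptogenic foci cannot be accurately located or multiple epileptogenic foci are suspected after a comprehensive evaluation". Table 1 shows one eligibility screen, in the enrolment column (day −10). Randomisation is marked in the same column, and the operation is at day 0.

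**RF-TC arm.** "Patients enrolled in the stereotactic EEG-guided RF-TC group will undergo multicontact electrodes" implantation, and then "Intracranial EEG recordings will be monitored to locate the epileptogenic zone". A test heating follows, with a further condition: "If the patient does not experience any unacceptable complications, RF-TC will be proceeded".

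**Other arms.** Resection goes straight to the operation: "Patients with temporal lobe epilepsy will undergo standard anterior temporal lobectomy", with lesionectomy and corticectomy for extratemporal cases. Laser ablation (LITT) is planned on CT, "fused with T1-weighted MRI by the Sinoplan (V2, Sinovation, China) software for robot navigation registration". Neither section describes intracranial recording.

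**Follow-up and analysis.** Under Procedures for withdrawal or discontinuation, visits at 3, 6 and 12 months continue until one of several listed events. Two of these are the investigator's judgement that the participant should stop and the need for other epilepsy surgery. Statistical analysis says the primary outcome is analysed by intention-to-treat.

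**The concern.** The same question, where the zone is, is answered before randomisation for everyone and then asked again after allocation, as described, in one arm only. The Background credits stereo-EEG with "pinpointing the epileptogenic network that no other noninvasive examination can provide", so the authors themselves expect it to show things that the earlier work-up may not. Some RF-TC patients may therefore prove to have a different, a second or an unlocatable focus. Equally affected patients in the other arms would not be identified in this way.

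What matters is what happens next. A discordant finding could prompt either of the two stopping events above, possibly before any lesion is made, and the decision would be taken by clinicians who know the allocation. The primary outcome needs a postoperative seizure frequency at each visit, so once visits stop there is nothing to analyse. If these patients tend to do worse, their loss would make lesioning look better against resection.

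**Working it through.** **1. Patients exposed to the extra step.** The protocol's own figures are 240 patients, 1:1 lesioning to resection, and 4:1 RF-TC to LITT within lesioning.

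- Resection: 240 × 0.5 = 120
- RF-TC: 120 × 0.8 = 96
- LITT: 120 × 0.2 = 24

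The step therefore concerns 96 of 240 patients, and 80% of the lesioning arm.

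**2. The route from finding to missing outcome.**

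| Step | Section | Stated or inferred |
|---|---|---|
| Definite zone settled before randomisation | Abstract (Methods); Participant selection; Table 1 | Stated |
| Zone located by intracranial EEG after allocation | Arm 2 | Stated |
| No such step in resection or LITT | Arms 1 and 3 | Not described there |
| Some findings discordant | Background, on what stereo-EEG adds | Plausible; no rate given |
| Investigator stops the patient, or other surgery is needed | Withdrawal or discontinuation | Possible; not tied to EEG findings |
| Visits then end | Withdrawal or discontinuation | Stated |
| Patient still belongs to the analysis set | Statistical analysis | Stated |

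The last two rows are in tension. Intention-to-treat says who is analysed. It cannot supply measurements that another section has stopped collecting.

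**3. Illustrative size.** None of the following values comes from the protocol. Assume mean remission m = 60% in every arm, d = 20% in discordant patients, a fraction q of RF-TC patients found discordant, all of them lost, and equally affected patients retained in the other arms. With s = 0.8, the RF-TC share of the lesioning arm:

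Gain in the pooled lesioning mean = s·q·(m − d) / (1 − s·q)

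- q = 5% (about 5 patients): 0.04 × 40 / 0.96 = 1.67, so 60% becomes about 61.7%.
- q = 15% (about 14 patients): 0.12 × 40 / 0.88 = 5.45, so 60% becomes about 65.5%.
- q = 15%, but a random half of the discordant patients lost: 0.06 × 40 / 0.94 = 2.55.
- Any q, none lost: 0.

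Direct check at 15%: the remaining RF-TC mean is (60 − 0.15 × 20) / 0.85 = 67.06 in 81.6 patients. Pooled with 24 LITT patients at 60, this gives (81.6 × 67.06 + 24 × 60) / 105.6 = 65.5.

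**4. A harsher set of assumptions.** Take a 60% success rate in all other lesioning patients and 0% in those lost. The inflation is then 0.6 × 96q / 120, or 1.0, 2.4, 4.8 and 9.6 points at q = 2%, 5%, 10% and 20%.

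**5. Scale.** The Sample size section gives a noninferiority limit of 10% but does not say that it applies to mean remission. It serves here only as a yardstick. The same section's 20% withdrawal allowance protects the number of evaluable patients. It does not protect comparability when the losses are related to arm and prognosis.

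**The case against.** A reader might infer that RF-TC patients with discordant recordings are declared ineligible and dropped in that arm alone. The documents do not support this. Eligibility is fixed before randomisation by the abstract and by the single screen in Table 1. No section makes an intracranial EEG finding a ground for exclusion. The stopping rules apply to all arms, govern visits rather than the analysis set, and do not mention localisation. Intention-to-treat is stated.

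Three further points deserve weight.

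- The Arm 2 text can be read as choosing contacts within a zone already defined, as part of the assigned treatment. It goes on to apply RF-TC to the contacts of that zone. The wording is nevertheless that recordings locate the zone, and if contact selection is meant, one sentence would settle it.
- Intracranial recording outside the RF-TC arm is not ruled out. The Background classes electrode implantation as diagnostic surgery, only earlier operations to treat epilepsy are excluded, and surgical technique is referred to cited work. It therefore cannot be said that such patients could never be detected in the other arms.
- The handling of missing data may be in a full protocol or analysis plan that is not shown.

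The first two limit how firmly the asymmetry can be asserted. The third does not dispose of the point. The rule that ends visits is stated here, and an analysis method can only partly repair outcomes that were never collected.

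**Conclusion.** The point holds in a limited form and should be corrected. As described, RF-TC alone gains localising information after allocation, nothing says how a discordant result is handled, and the stopping rules, followed as written, could end outcome collection for patients whom the intention-to-treat analysis must include. Such losses could be related to both arm and prognosis.

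Under the 20% and 60% assumptions with every discordant patient lost, the distortion is about 1.7 points at 5% discordance and 5.5 points at 15%, in favour of lesioning. It shrinks in proportion as fewer are lost and is zero with complete follow-up. The direction depends on discordant patients doing worse than average, which is also an assumption. Confidence is medium, because discontinuation of these patients is permitted by the text rather than stated in it.

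**What to change.** Reconcile Participant selection, Procedures for withdrawal or discontinuation, the Arm 2 description and Statistical analysis:

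1. **Participant selection:** state that both localisation criteria are judged once, on the evaluation completed before randomisation, and record the target zone on the eligibility form at that time.
2. **Arm 2:** state that an intracranial EEG finding after randomisation does not reopen eligibility. If the recording only selects contacts within the recorded zone, say so.
3. **Withdrawal or discontinuation:** separate stopping treatment from stopping follow-up. A post-randomisation intracranial EEG finding, not receiving the assigned lesion, or other epilepsy surgery should not end outcome visits. Before the 12-month visit, only death, withdrawal of consent or loss of contact should do so.
4. **Statistical analysis:** state that these patients are analysed as randomised, with outcomes to 12 months.

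The cost is amendment wording, one form field and a little more follow-up work. The RF-TC result may look less favourable, because patients whose localisation changed stay in it. None of this prescribes when intracranial EEG is performed or how a discordant patient is treated; those remain clinical decisions.
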